**University of Exeter Qualtrics page suicide risk automated message:**

**“Your responses to these questions suggest you have been thinking about suicide or about hurting yourself.**

These kinds of thoughts can vary a lot. This may have just been a brief passing thought or reflect a sense of feeling trapped, but without any intention to do anything. These thoughts are relatively common and not that unusual in people who feel down or stressed. If you would like support with these thoughts, please contact your GP or relevant medical professional.

**If you feel at high risk to yourself or others, please contact your GP immediately.**

**You can contact your GP** using the normal telephone number for your GP practice. If the surgery is not open, you will either be automatically redirected to the out-of-hours GP service, or you will be given another number to call. You can also **phone 111 to access the NHS 111 service**, which provides access to local NHS healthcare services in England, and is available 24 hours a day, 365 days a year.

However, you may have been thinking about your death a lot, having persistent thoughts about killing yourself, experiencing suicidal intentions and urges, or be making plans to end your life. In any of these cases or if you have any other thoughts of suicide, we strongly recommend that you contact your general practitioner or family doctor **RIGHT AWAY** for advice and tell them how you are feeling

**If you don't think you can stay safe**, please go to the nearest hospital accident and emergency room. If none of these options are available, please contact a family member or a trusted friend, so that you won't be alone right now. It’s important to seek out the company of people who can support you and who will help to keep you safe.

Try to commit to a plan of action that does not involve suicide. If you have items that may be dangerous for you at home, please consider giving them to a trusted friend, neighbour, the police or a pharmacist for safekeeping until you feel stronger. Try to minimise the use of alcohol or illicit drugs, as using these substances are likely to make your recovery harder. It can also be helpful to think about your faith, loved ones, family and pets. It is important to remember that these feelings and urges do pass, and when individuals feel better, they are glad that they did not act on them. There are effective treatments that can help, and there is no need to struggle alone. Talking to people who understand can make it much easier to manage your symptoms so do please call one of the specialist helplines above. There may be reasons for hope that you have yet to consider. Sometimes the smallest reasons for living can get you through a difficult time. Having thoughts of suicide is nothing to be ashamed of and we encourage you to seek help.

Because the study is focused on managing excessive worry or low mood rather than treating current difficulties, this study is not suitable for you. The Iona mobile phone app has not been designed to help with these difficulties so we are sorry to say that taking part in the study would not be in your best interests at this time. Thank you for your interest.

**We strongly recommend contacting your GP or family doctor as the best person to decide what help you need**.

In addition to your GP or if you don’t feel that you can talk to your GP, there are many useful services and useful sources of support.

We hope that you find one or more of the following helpful:

- **Emergency Services** If you need help and it’s an emergency call: 999
- **NHS 111** If you need help now and its not an emergency call: 111
- **Op Courage** An NHS mental health specialist service designed to help serving personnel due to leave the military, reservists, armed forces veterans and their families. Contact: [[contact]](mailto:[contact]) Call: [name]
- **Papyrus [name] or text: [name]** offers National support to young people up to age 35 who are feeling suicidal. (Monday-Friday 10:00am-5:00pm and 7:00pm-10:00pm; 2:00pm-5:00pm on weekends, [[contact]](mailto:[contact])
- The **Samaritans** **[name]**  Freephone (UK and Republic of Ireland): [name] (24 hours) offer a confidential service so you can talk about your feelings, you can contact them at [www.samaritans.org](http://www.samaritans.org), Email: [[contact]](mailto:[contact])
- **SANE** offers support to anyone coping with mental illness, including concerned relatives or friends. The SANE helpline **[name]** is available 7 days a week from 6.pm-11 pm
- **Maytree** is a registered charity supporting people in suicidal crisis and is open for calls and emails 24 hours a day. **– [name],** [[contact]](https://www.bipolaruk.org/)
- There are a series of NHS self-help guides which can be found here <https://web.ntw.nhs.uk/selfhelp/>
- There are more guides and online courses here: <https://www.cci.health.wa.gov.au/Resources/Looking-After-Yourself>

In the event a participant indicates suicide risk at end of treatment or 6 week follow up (10 weeks) and this screen is displayed, an automated report/record from the website will be sent to the Lead Researcher and logged by them. The record will show the trial number and the answers to the 3 risk questions. This data will monitor frequency of suicidality across the trial arms.

### 13.5 For participants reporting significant levels of depression at any of the follow-up assessments (defined as PHQ-9 score >20)

The follow-up website will automatically provide them with the following information:

**Follow-up Website Automated message for depression:**

**“Your responses to these questions suggest that within the last month, your overall mood has been low for at least 2 weeks and has had a negative effect on your life. It may be that you are currently experiencing an episode of depression or going through a period of stress or loss.**

If you currently are having problems with the symptoms of depression then **we strongly recommend that you talk to your general practitioner, family doctor or a mental health professional** about your difficulties, as he or she may be able to find ways to help you to improve your mood and handle life’s difficulties better.

If you have not had a health check recently that may also be worth doing so. If you have a diagnosis of depression, please make sure that you follow your treatment regime and consult with the medical professionals involved in your care.

**You can contact your GP** using the normal telephone number for your GP practice. If the surgery is not open, you will either be redirected automatically to the out-of-hours GP service, or you will be given another number to call. You can also **phone 111 to access the NHS 111 service**, which provides access to local NHS healthcare services in England, and is available 24 hours a day, 365 days a year.

As well as your GP, there are many other services available who are really experienced at helping people with your symptoms:

Here are some useful websites that you access directly:

- The **Samaritans** **[name]**  Freephone (UK and Republic of Ireland): [name] (24 hours) offer a confidential service so you can talk about your feelings, you can contact them at [www.samaritans.org](http://www.samaritans.org),
- There are a series of NHS self-help guides which can be found here <https://web.ntw.nhs.uk/selfhelp/>
- There are more guides and online courses here: <https://www.cci.health.wa.gov.au/Resources/Looking-After-Yourself>
- **Mind** The Mental Health Charity provide information, advice, and support to empower anyone experiencing a mental health problem. They provide information about mental health problems and potential treatments as well as tips for everyday living. [https://www.mind.org.uk/](mailto:[contact])
  - **For info about depression:** <https://www.mind.org.uk/information-support/types-of-mental-health-problems/depression/#.XGQRn1X7SUk>
  - **For apps to help with your mental health and wellbeing:** [https://www.mindcharity.co.uk/advice-information/how-to-look-after-your-mental-health/apps-for-wellbeing-and-mental-health/](https://www.rethink.org/media/1020652/ResourceFinal.pdf)
- **Rethink Mental Illness** Provide expert advice and information to everyone affected by mental health problems, and provide services and groups; [https://www.rethink.org/living-with-mental-illness/](https://www.mindcharity.co.uk/advice-information/how-to-look-after-your-mental-health/apps-for-wellbeing-and-mental-health/)
- **There are a series of NHS self-help guides which can be found here** [https://web.ntw.nhs.uk/selfhelp/](https://youngminds.org.uk/find-help/)
- **There are more guides and online courses here:** <https://www.cci.health.wa.gov.au/Resources/Looking-After-Yourself>

**Helplines**

Alternatively, here are helplines you can ring to talk to someone about what you’re going through:

We hope that you find one or more of the following helpful:

- **NHS 111** If you need help now and it’s not an emergency call: 111
- **Op Courage** An NHS mental health specialist service designed to help serving personnel due to leave the military, reservists, armed forces veterans and their families. Contact: [[contact]](mailto:[contact]) Call: [name]
- **Papyrus [name] or text: [name]** offers National support to young people up to age 35 who are feeling suicidal. (Monday-Friday 10:00am-5:00pm and 7:00pm-10:00pm; 2:00pm-5:00pm on weekends, [[contact]](mailto:[contact])
- The **Samaritans** **[name]**  Freephone (UK and Republic of Ireland): [name] (24 hours) offer a confidential service so you can talk about your feelings, you can contact them at [www.samaritans.org](http://www.samaritans.org), Email: [[contact]](mailto:[contact])
- **SANE** offers support to anyone coping with mental illness, including concerned relatives or friends. The SANE helpline **[name]** is available 7 days a week from 6.pm-11 pm
- **Maytree** is a registered charity supporting people in suicidal crisis and is open for calls and emails 24 hours a day. **– [name],** [[contact]](https://www.bipolaruk.org/)
- **Papyrus [name] or text: [name]** offers National support to young people up to age 35 who are feeling suicidal. (Monday-Friday 10:00am-5:00pm and 7:00pm-10:00pm; 2:00pm-5:00pm on weekends, [[contact]](mailto:[contact])
- The **Samaritans** **[name]**  Freephone (UK and Republic of Ireland): [name] (24 hours),offer a confidential service so you can talk about your feelings, you can contact them at [www.samaritans.org](mailto:[contact]), Email: [[contact]](https://www.studentsagainstdepression.org/)
- **SANE** offers support to anyone coping with mental illness, including concerned relatives or friends. The SANE helpline **[name]** is available 7 days a week from 6.pm-11 pm
- **Maytree** is a registered charity supporting people in suicidal crisis and is open for calls and emails 24 hours a day. **– [name],** [[contact]](https://www.mind.org.uk/information-support/types-of-mental-health-problems/bipolar-disorder/about-bipolar-disorder/)
- **The Mix**, Freephone: [name] (13:00-23:00 daily), If you're under 25 you can talk to The Mix for free on the phone, by email or on their webchat. You can also use their phone counselling service, or get more information on support services you might need. [www.themix.org.uk](http://www.themix.org.uk/)

Talking to people who understand can make it much easier to manage your symptoms so **please do call your GP or one of the specialist helplines above**.

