### 13.1.2 Risk management in trial

Once the participant joins the study and starts to use either of the apps, risk is managed by the participant selecting the SOS button or being directed to the SOS button in the event that either PHQ-9 has increased >1 or score has increased >20. Each occurrence of elevated symptomatology (PHQ-9>20) or risk (PHQ-9-Q9>1) when using either app will be logged by the electronic system, the Lead Researcher notified and recorded as an AE.

We note that the nature of the high level of confidentiality means that we do not have relevant GP or family doctor details for participants. The default response is direct information disclosure to the participant of a potential clinical issue with signposting information provided. Transmission of the collected information to the GP will not be possible and requesting this information a priori would negate the ethical and recruitment benefits of pseudo-anonymity and confidentiality for participants. Based on recent recommendations, our default policy is to inform participants of the possibility of them being at risk and to recommend they seek help. This is to prioritise their welfare.

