### 13.2 Preventing abuse of participants and risk analysis

Our risk analysis indicates potential theoretical risks and opportunities for abuse of the research findings and of participants within the study including psychological harms (e.g., distress), invasion of privacy (e.g., intrusion into private affairs, public disclosure of embarrassing private information, publicity that puts the individual in a false light to the public, or appropriation of an individual’s name or picture for personal/commercial advantage), loss of confidentiality (personal data becoming public through error or thorough deliberate hacking), and social harms (e.g., embarrassment, stigmatisation). The risk analysis indicates that the likelihood of these risks occurring is relatively low although any potential impact for participants would be high, and, as such, we will enact a detailed participant risk register and update it regularly through the project. Multiple steps and processes will be put into place to mitigate and minimise these risks including (a) explaining potential risks in the information sheet; (b) the welfare procedures described above to minimise participant distress; (c) high levels of security and the use of privacy by design protocols for the app and database; (d) a privacy impact assessment; (e) the emphasis on confidentiality in the project and the separation of collected data from personal identifiers; (f) the use of a code of conduct for all researchers.

In this trial no medical care is provided regardless of the level of risk presented. This is because this trial is for people seeking to manage low mood or excessive worry in a self-help intervention for people with no current risk or have experienced a traumatic episode in the last month. Participants are advised of this at the beginning of the respective app, on the information sheets and sign the section on the Consent Form to confirm that they understand this.

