### 13.4 University of Exeter Qualtrics page at second screening (as baseline), 6 and 10 week follow up

A recruit may indicate risk on the website during the baseline assessment or 6 weeks treatment end or 10 weeks follow up in response to questions about suicidality. If the participant scores 2 or 3 on the PHQ-9 Q9, the participant will be encouraged to seek support from family or friends, GP or signposting information to NHS or female Armed Forces signposting information will be provided.

PHQ-9-Q9

Over the last two weeks, how often have you been bothered by any of the following problems? Thoughts that you would be better off dead, or of hurting yourself in some way?

Those scores would represent the answers several days (1), more than half the days (2) and nearly every day (3)

If the potential participant answers yes to either more than half the days (2) or nearly every day (3) to either question, then they would be removed from the trial and automatically presented with the following risk screen:

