  - **Toolkit for young people with questions or worries about their mental health:** [https://www.rethink.org/media/1020652/ResourceFinal.pdf](http://www.samaritans.org)
- **There are a series of NHS self-help guides which can be found here** <https://web.ntw.nhs.uk/selfhelp/>
- **There are more guides and online courses here:** <https://www.cci.health.wa.gov.au/Resources/Looking-After-Yourself>

Alternatively, here are **HELPLINES** you can ring to talk to someone about what how you are feeling

- **Papyrus [name] or text: [name]** offers National support to young people up to age 35 who are feeling suicidal. (Monday-Friday 10:00am-5:00pm and 7:00pm-10:00pm; 2:00pm-5:00pm on weekends, [[contact]](https://www.mind.org.uk/information-support/types-of-mental-health-problems/psychosis/)
- The **Samaritans** **[name]**  Freephone (UK and Republic of Ireland): [name] (24 hours),offer a confidential service so you can talk about your feelings, you can contact them at [www.samaritans.org](https://exeter.content.minddistrict.com/contentresources/0e83f1018dfc42778b169c48491b6de3/resources/out_of_hours_leaflet_uk.pdf), Email: [[contact]](https://youngminds.org.uk/find-help/)
- **SANE** offers support to anyone coping with mental illness, including concerned relatives or friends. The SANE helpline **[name]** is available 7 days a week from 6.pm-11 pm
- **The Mix**, Freephone: [name] (13:00-23:00 daily), If you're under 25 you can talk to The Mix for free on the phone, by email or on their webchat. You can also use their phone counselling service or get more information on support services you might need. [www.themix.org.uk](https://www.rethink.org/media/1020652/ResourceFinal.pdf)

If you find your symptoms particularly distressing or have thoughts about ending your life then please go to the nearest emergency room, or immediately contact your GP.

Talking to people who understand can make it much easier to manage your symptoms so **please do call your GP or one of the specialist helplines above**.

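### The automated message for a follow-up PHQ-9 above 20 (Protocol 13.5) gives no emergency route, although the messages in 13.4 and 13.6 do

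*Protocol*

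**What the plan says.** Protocol Section 13.5 applies to participants reporting significant depression "at any of the follow-up assessments (defined as PHQ-9 score >20". The follow-up website then shows a fixed message. It points to the GP, the out-of-hours GP service, NHS 111, several websites and a list of helplines. In that list the NHS 111 entry reads "If you need help now and it’s not an emergency call: 111". The message closes by sending the reader back to her GP or the helplines.

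Two other automated messages are given in full:

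- **Section 13.4 (suicide risk).** The condition is "If the participant scores 2 or 3 on the PHQ-9 Q9". The text tells a woman who cannot stay safe "please go to the nearest hospital accident and emergency room", and its helpline list opens with "If you need help and it’s an emergency call: 999", followed directly by the NHS 111 entry.
- **Section 13.6 (bipolar disorder or psychosis, excluded before consent).** The text ends by telling anyone in marked distress or with thoughts of ending her life "please go to the nearest emergency room, or immediately contact your GP".

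On what stands behind these messages, Section 13.1.2 states that "we do not have relevant GP or family doctor details for participants", and Section 13.2 states: "In this trial no medical care is provided regardless of the level of risk presented".

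**The concern.** The 13.5 list keeps the non-emergency half of the 999/111 pair in 13.4 and drops the emergency half. No reason is given. Redaction does not explain it: 999 and 111 are both legible in 13.4, and 13.5 has no emergency-services entry at all.

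The protocol itself treats a score in this range as raised risk. A PHQ-9 of 20 or more excludes at entry (Section 7), a score above 20 counts as a sign of distress (12.2), and it is logged as an adverse event (13.1.2). The 13.5 helpline list includes services for people who are suicidal or in suicidal crisis, so it expects some readers to be in that state.

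With no clinical care in the trial and no GP to contact, the automated wording is one of the few safeguards a flagged participant meets. As written, a woman excluded under 13.6 before joining is told about the emergency room, while an enrolled woman who has worsened past 20 with item 9 at 0 or 1 is not.

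**Working it through.** The plan states no figure to reproduce. The check has two parts.

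**1. Emergency routes in each message** (999, A&E, emergency room, hospital or emergency services):

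| Message | Trigger | 999 | A&E or emergency room | Total |
|---|---|---|---|---|
| 13.4 | Item 9 = 2 or 3 | yes | yes | 2 |
| 13.5 | PHQ-9 total > 20 at follow-up | no | no | 0 |
| 13.6 | Self-reported bipolar disorder or psychosis | no | yes | 1 |

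**2. Can someone receive 13.5 without 13.4?**

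Inputs: PHQ-9 has nine items, each scored 0 to 3 (Table 11); 13.5 needs a total above 20, so at least 21; 13.4 needs item 9 = 2 or 3; entry needs a total below 20, so at most 19, with item 9 at most 1 (Table 8).

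- Maximum from the eight items other than item 9: 8 × 3 = 24.
- Item 9 = 0: the total can reach 24 + 0 = 24, so 21 to 24 triggers 13.5 alone. The other eight items must sum to at least 21 of 24.
- Item 9 = 1: the total can reach 24 + 1 = 25, so 21 to 25 triggers 13.5 alone. The other eight items must sum to at least 21 − 1 = 20 of 24.
- Smallest rise from entry that triggers 13.5: 21 − 19 = 2 points.

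The two triggers therefore separate. The group that sees only 13.5 includes women reporting thoughts of death or self-harm on several days (item 9 = 1), and a small worsening from the top of the entry range is enough to reach the threshold.

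**The case against.** The best case against the point runs as follows.

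- **The messages are graded by purpose.** 13.4 deals with suicide risk and 13.5 with symptom severity. Item 9 = 1 is allowed at entry, so the protocol does not treat that answer as raised risk. This explains why 13.5 leads with the GP and NHS 111. It does not explain dropping 999 from a list that otherwise serves people in crisis.
- **The 13.4 trigger is loosely worded.** The section also refers to either question, and later to three risk questions, so other items might trigger it. But item 9 is the only item the section names.
- **The 13.6 comparison is imperfect.** Its emergency sentence is conditional, it addresses a different group, and it does not list 999. That is fair, but the contrast with 13.4 is enough by itself.
- **Other cover exists.** 13.5 gives NHS 111, Samaritans and Maytree around the clock. Sections 12.2 and 13.1.2 add the SOS button, logging, notification of the Lead Researcher and adverse-event recording. This is real mitigation. However, logging and notification do not direct the participant anywhere. The SOS text is not reproduced, so it cannot be shown either to contain or to lack an emergency route. SOS is also an app function, whereas the follow-up message appears on a website.
- **Few people are affected.** This is probably right, and it limits the expected number without changing what an affected woman is shown.

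**Conclusion.** The point holds. The 13.5 message contains no emergency route, against two in 13.4 and one in 13.6. The practical gap is confined to participants with a follow-up total of 21 to 24 and item 9 at 0, or 21 to 25 and item 9 at 1; those with item 9 at 2 or 3 also meet the 13.4 condition and its emergency advice.

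This rests on two assumptions: that item 9 alone triggers the 13.4 message, as the section's only defined condition says, and that the message is used as printed. How often it would happen cannot be estimated from the protocol; among 60 randomised it may be few. It is a participant-safety wording gap that touches no endpoint or analysis. It should be corrected because the consequence for one affected woman could be serious and the remedy is trivial.

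**What to change.** Add two pieces of existing 13.4 text to the 13.5 message: the 999 entry, placed immediately before the NHS 111 entry in the helpline list, and the sentence sending anyone who cannot stay safe to A&E, placed ahead of the helplines. Have the wording confirmed by a clinically responsible member of the team, for example the co-investigator who advised on the signposting contacts (Section 8.2). It would be sensible to check at the same time that the SOS screen carries the same two routes.

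The cost is two lines copied into one automated message. Data collection, analysis and sample size do not change.
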